## Abstract

**Background:**

Children with cerebral palsy (CP) have life-long motor disorders, and they are typically subjected to extensive treatment throughout their childhood. Despite this, there is a lack of evidence supporting the effectiveness of early interventions aiming at improving motor function, activity, and participation in daily life. The study will evaluate the effectiveness of the newly developed Small Step Program, which is introduced to children at risk of developing CP during their first year of life. The intervention is based upon theories of early learning-induced brain plasticity and comprises important components of evidence-based intervention approaches used with older children with CP.

**Method and design:**

A two-group randomised control trial will be conducted. Invited infants at risk of developing CP due to a neonatal event affecting the brain will be randomised to either the Small Step Program or to usual care. They will be recruited from Astrid Lindgren Children’s Hospital at regular check-up and included at age 3–8 months. The Small Step Program was designed to provide individualized, goal directed, and intensive intervention focusing on hand use, mobility, and communication in the child’s own home environment and carried out by their parents who have been trained and coached by therapists. The primary endpoint will be approximately 35 weeks after the start of the intervention, and the secondary endpoint will be at 2 years of age. The primary outcome measure will be the Peabody Developmental Motor Scale (second edition). Secondary assessments will measure and describe the children’s general and specific development and brain pathology. In addition, the parents’ perspective of the program will be evaluated. General linear models will be used to compare outcomes between groups.

**Discussion:**

This paper presents the background and rationale for developing the Small-Step Program and the design and protocol of a randomized controlled trial. The aim of the Small Step Program is to influence development by enabling children to function on a higher level than if not treated by the program and to evaluate whether the program will affect parent’s ability to cope with stress and anxiety related to having a child at risk of developing CP.

**Trial registration:**

ClinicalTrials.gov Identifier NCT02166801. Registered June 12, 2014.

## Background

Cerebral Palsy (CP) is a result of a spectrum of early acquired disturbance to the developing brain. The brain abnormalities or insults that cause CP can appear at different time points during pregnancy and in the neonatal period [1]. To date, there are no biological or pharmacological treatments. However, neurobiological research suggests that the effectiveness of the neural networks and pathways can be strengthened by early interventions. Despite the rather large population of individuals with CP world-wide, there is still a lack of evidence-based early intervention programs that make it possible to utilize the therapeutic window that the rapid brain development and adaptability of the central nervous system during the first year of life represents [2, 3]. This paper describes the rationale, contents, and structure of the *Small Step Program*, an early intervention program for children at risk of developing CP. The Small Step Program was designed to provide individualized, goal directed, and intensive intervention within three distinct foci (hand use, mobility, and communication) in the child’s own home environment and carried out by their parents who have been educated and coached by therapists.

A plausible reason for the lack of effective early intervention programs for children at risk of developing CP is the common “wait and see” approach due to the uncertainty of early diagnostic criteria [3]. There is a wide range of factors, very often in combination, that can be the cause of the early insult to the developing brain that will result in the diagnosis of CP [4–6]. Highly individual developmental trajectories of postural control, motor function, and muscle tone that vary considerably during the first years are frequently seen in children at risk of developing CP. In addition, risk factors and signs of CP might be visible at a very early age but might not necessarily lead to CP. A child with delayed development might recover and atypical signs might disappear, and the opposite can occur in which a child develops CP without obvious early signs. Thus, there is the dilemma in that the potential effect of early intervention might be lost if we wait with intervention until the CP diagnosis has been confirmed. Although the ability to predict the risk of developing CP at an early age has increased when using a combination of general movement assessments, neurological examinations, and brain imaging techniques [7, 8]. Different brain structures are more susceptible to injury during certain time periods during pregnancy. An early insult during the first trimester can lead to a maldevelopment of the brain, while the white matter, particularly in areas close to the ventricles, is more vulnerable to injury in the late second to early third trimester. An insult close to term causes predominantly cortical and subcortical grey matter lesions (e.g. injuries involving the thalamus and basal ganglia) [9, 10]. The timing of the brain disturbance, in addition to its size and location, has been reported to be closely related to the severity of motor impairments [9, 11]. The effects of specific disturbance characteristics on motor development are understood to some extent; however, very little is known about the relationship between the timing and extent of the lesion and the effects of early interventions.

### Evidence for the efficacy of early intervention

Early intervention, carried out during the first year in life when the brain is under rapid development and most plastic, is assumed to be more effective than intervention later during development or in adulthood. This assumption is based on the knowledge that neural networks and pathways that remain intact after brain injury can be strengthened through learning-induced plasticity. Recent animal studies have suggested that there is a critical period of motor system plasticity and that activity-dependent reorganisation of the corticospinal motor-projection pattern to the hand occurs before 1 year of age [12, 13].

The potential of early interventions is well founded in experimental research, while clinical studies on physiotherapy for infants with CP, or children with high risk for CP, have not been able to show positive changes on motor development that exceed the expected developmental trajectory [14–17]. It seems that the concept of enriched environments based on great developmental effects in animal research can be transformed to children [18]. A recent pilot study using enriched environments to elicit self-initiated motor behaviours; including parent training and task analysis for frequent practice – has shown promising results [19]. Another recent early intervention study – COPing with and CAring for Infants with Special Needs (COPCA) – although vague results, is also of interest. COPCA is built of modern theories of brain development and uses the neuronal group selection theories framework in a family-centred approach [20]. There is some evidence indicating that more specific training might lead to a more favourable outcome when compared to general training [15]. For example, training approaches targeting other areas than overall motor development, such as cognition, seem to have positive results, at least in a short-term perspective, in preterm children [16, 21]. Early intervention directed towards communication is also known to have a positive influence on cognitive and pre-linguistic development and to result in more advanced communication in preterm children in a short term perspective [22]. When it comes to interventions targeting hand function, there is no specific intervention program developed for children with a high risk of developing CP. However, for children with unilateral CP, there are studies indicating that Constraint-Induced Movement Therapy (CIMT) can be adapted and used for infants and that this can increase the odds of having a higher functional level when the training is introduced within the first year of life [23]. From a family perspective, it is also of interest to highlight that early interventions have been shown to facilitate bonding and to reduce parental stress [8, 24]. These positive changes following intervention within the areas of cognition, communication, and attachment provide an interesting and promising contrast to the absence of improvements in overall motor development following intervention for infants. This is especially the case because there are high levels of evidence for several different treatment approaches aiming to improve motor function in older children [17]. Thus, there is a great need to develop new methods to improve models for early interventions in younger children and infants at high risk of developing CP.

### Theoretical background for the small step program *–* the child’s perspective

The Small Step Program is an individualized, goal directed, and intensive intervention that focuses on hand use, mobility, and communication. The program is intended to be carried out in the child’s home environment and be conducted by their parents who are trained and coached by therapists. The program is designed be used from about 4 months of age and seeks to take advantage of the theoretically plastic period of brain development at this age. The program is designed to include and combine components that are known to be of importance in evidence-based intervention approaches for older children. The challenge in the Small Step Program is to adapt this knowledge and apply it within an intervention for very young children.

The goal-directed approach has been successfully used in older children [25, 26]. However, for families in a very vulnerable time period of life, with a young infant with high risk of developing CP, it is not easy to define goals in either the short or long-term perspective. In a goal-setting approach, the person’s own individual wishes are a strong ingredient, and it is suggested that the goals should be functional and meaningful for daily life [27]. Such a goal-centred approach is taken in the Small Step Program, and collaboration between the parents and therapists will help the family to determine and focus on what their infant will likely be able to learn as a next step within the different foci and to define goals that are closely related to the child’s ability and cognitive level.

Within the Small Step Program, great emphasis is put on children’s self-initiated actions, which are stimulated by meaningful and motivating activities and toys [28, 29]. The stimuli should be clear and understandable for the child and should be related to the child’s developmental stage. It is assumed that development is driven by children’s unique characteristics and capacity to explore a situation through which they discover new and more advanced activities. Therefore, the training should be conducted at a level that is challenging, but not too demanding, i.e. the training should fall within the zone of proximal development, ZPD [30]. The scaffolding and shared attentional focus provided by the ZPD aims to ensure that the child’s interest is maintained for as long as possible, which will promote the internalisation of independent developmental achievements. This concept is commonly applied within motor learning programs. The challenge here lies in helping parents understand how self-initiated actions can be promoted for infants with a very low ability level.

Another important principle of the program is the concept of repetition and extensive practice. It is well established that a task has to be well learned if it is to be performed effectively. Thus, it must be possible even for infants to experience that a particular task can be performed with ease and success, such as grasping a toy or keeping control of their gaze. When Adolph and colleagues studied factors that could explain the rate of improvement when toddlers with typical development learn to walk, the only significant factor found was the amount of experience and practice that children had [31]. In the Small Step Program, we commonly use the word training, and in this sense it is synonymous to practice. It has to be emphasized that training can only be performed as long as the infant finds it enjoyable because infants cannot be forced to perform self-initiated actions. One of the overarching goals with the Small Step Program is thus to create a positive reflective atmosphere that promotes self-initiated actions and communication and communication in the child’s home environment. Maximizing the frequency of self-initiated motor activity in the child’s everyday environment has been suggested to be the most crucial factor supporting motor learning [32].

The rationale for dividing the intervention program into the three focus areas of hand use, mobility, and communication is to facilitate the learning process within each area. Typically, a child learns a lot within each area during the first year of life, and each focus area includes a huge amount of competence for parents as the training providers to capture. There is a limited amount of time during the day when a small child can attend to practice because caring and sleeping usually predominate their days. By introducing specific foci, we intend to help the family to optimize the training and to use their time as efficiently as possible. The *hand-use* focus will be used to help the child explore their external world through object manipulation, and this creates an important link to the child’s cognitive development. Knowledge about fine motor development and object exploration will guide the introduction of new activities. Voluntary action starts to emerge at birth, and von Hofsten and Lindhagen have demonstrated that reaching and grasping actions can be detected even in new-borns, though it takes some months before grasping actions are obvious and frequent [33]. In the first year of life, infants gradually gain remarkable control over their hands, and they begin exploring and manipulating objects with increasing skill [34, 35]. The *mobility* focus will be used to reach new gross motor ability goals with the overall aim that children should be able to move about and explore their external world on their own. This includes activities like maintaining and changing body position, sitting and standing, and any other form of mobility. The principles for reaching goals will be based on matching the child’s present capacity and environment with the target actions [36]. As a consequence, motor learning will not be expected to occur in the same order as in children with typical development. However, we do expect accelerated motor development to occur because there is a rapid pace during the first year of life during typical development. The *communication* focus will be used to enhance sensitive parental communication strategies that support child-centred interactions and child initiatives. The infants’ early communication skills will cover a wide range of behaviours such as crying, body movements, gestures, and directed gaze. These communication signals are the foundation for later linguistic skills and cognitive development. An important landmark to develop is shared focus or joint attention, i.e. the mutual attention between the infant and the parent. A particularly important form of joint attention is triadic engagement in which the infant can alternate his/her gaze between the parent and an outside object or event. Joint attention forms both a cognitive as well as a socio-emotional foundation for the child’s learning during activities and for their inter-personal engagement [37–39]. Raising awareness of the child’s communicative attempts and learning to respond and maintain communication will guide the training.

The intervention within the different foci will be further described in the methods section.

### Coaching, education, and collaboration with parents

Coaching of parents plays a prominent role in the Small Step Program. The aim is to provide a solution-focused approach that helps families to achieve goals that are unique and meaningful to them. There is at present no universal definition of coaching as a concept – definitions range from a relationship-directed to intervener-directed process – and there is no clear distinction between parent training and coaching [40]. Graham and colleagues’ definition of coaching contains emotional support, information exchange, and a structured process that includes elements such as goal setting, exploring options, planning actions, carrying out plans, checking performance, and generalizing. Furthermore, it is shown that the coach facilitates goal performance and supports parents in identifying ways to promote successful performance [41]. When coaching was used as a major strategy in a recent early intervention program (COPCA), it was defined as the promotion of creative exploration of the competencies of the family with the aim to encourage self-made decisions in everyday activities [42]. Further aspects that promote learning are presented by Turner and Paris, who emphasize the importance of motivation. They describe a model that supports learning called the “Six-C model” for choice, control, challenge, collaboration, constructive meaning, and consequence [43]. Although coaching is well established from a theoretical perspective, its effectiveness in practice has not been fully evaluated. A recent review summarizing the evidence for coaching’s effectiveness found only a few high-quality studies [44]. The most clear high-quality evidence was for improved educational outcomes for children at risk of developmental delay, but there was also some moderate evidence for improving motor outcome in children with CP if a motor learning approach is used. In the Small Step Program, we will take a broad approach to coaching and parent training. For the therapists coaching the parents to conduct the Small Steps training program, motivational interviews [45] and solution-focused coaching [32] are important tools.

## Methods and design

This paper describes the methodology of a randomised controlled trial comparing the effect of the Small Step Program with treatment as usual for children younger than 1 year of age who are at risk of developing CP or other neurodevelopmental disorders. The outcomes of this trial will be evaluated after 14 weeks of intervention, at the end of the study period (approximately 35 weeks after the start of the intervention) and when the children are 24 months corrected age.

### Primary and secondary objectives

The primary objective of this trial is to evaluate the effects of the newly developed Small Step Program on general development in children at risk for developing CP or other neurodevelopmental disorders. The main hypothesis of the study is that the Small Step Program is more effective than treatment as usual when children are evaluated at the age of 2 years. The rapid brain development and plasticity during the first year of life is utilized as a possible therapeutic window for intensive training. The design of the program, with three different foci during separate time periods, was designed in relation to the second hypothesis. We assume that children will have a more rapid development within the specific focus of each time period compared to the development rate within the other two foci that are not being trained at that particular time: i.e. you learn what you practice. The third hypothesis is that children’s ability to develop will be influenced by the specific characteristics of any underlying brain pathology.

The secondary objective is to evaluate the effect of the Small Step Program on parents’ ability to cope with the stress and anxiety related to the traumatic experience of parenting a child at risk of developing CP. The hypothesis is that parents in the Small Step Program will be less stressed and can better cope with their child’s situation than parents of children receiving usual care. Thus, the tools provided within the Small Step Program like coaching, supervision, education, and feedback on how to stimulate task performance and communication will make parents more able to cope with the child’s delayed development.

The study will be a randomised, controlled, prospective, parallel-group trial based on the Consolidated Standards of Reporting Trials (CONSORT) statement regarding the randomised trial of non-pharmacological treatments. Children will be randomised to one of two arms – the Small Step Program or treatment as usual. The children in the Small Step Program will be further randomised to start with either hand-use or mobility (Fig. 1). The rationale for the second randomisation is based on the *second* hypothesis.

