### Outcome measures and procedures

Children and parents in both groups will be assessed at the different endpoints (Fig. 1). The assessments are chosen based on the first aim of the study and to measure general and specific development and describe the characteristics of the brain lesion. Assessments chosen for the second aim evaluate the effects of the program on the parent’s perspective. The *Peabody Developmental Motor Scales, Second Edition (PDMS-2)* will be used as the primary outcome measure.

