## Statistical methods

Descriptive data for each outcome measure (primary and secondary) will be summarized and presented for both treatment groups (Small Step or treatment as usual). Changes over time and developmental trajectories will be investigated in both groups for each outcome measure with the use of mixed models, repeated-measures ANOVA, or corresponding non-parametric options depending on the data level and the distribution of data and in accordance with guidelines for RCTs. Post hoc analysis with correction for multiple comparisons will be applied when suitable. Group comparisons on all outcome measures will be made at 14 weeks and approximately 35 weeks after the start of the intervention and when the participants are 2 years old. All analyses will be conducted using IBM SPSS Statistics 22, and a significance level of *p* < 0.05 will be used.

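### The Abstract makes about 35 weeks the primary endpoint, but the objectives put the main hypothesis at 2 years, so the deciding comparison is not fixed

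*Protocol article*

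**What the plan says.** Two sentences of the protocol article bear directly on the point.

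- **Abstract, Method and design:** "The primary endpoint will be approximately 35 weeks after the start of the intervention", and "the secondary endpoint will be at 2 years of age".
- **Primary and secondary objectives:** the main hypothesis is that "the Small Step Program is more effective than treatment as usual when children are evaluated at the age of 2 years". This section ties no hypothesis to 35 weeks.

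The other relevant sections do not rank the time points.

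- **Methods and design:** "The outcomes of this trial will be evaluated after 14 weeks of intervention, at the end of the study period" (about 35 weeks), and at 24 months corrected age.
- **Outcome measures and procedures:** the PDMS-2 "will be used as the primary outcome measure", with no time attached.
- **Sample size:** 15 per group, raised to 24 per group, on PDMS-2 motor composite scores. It does not say at which visit.
- **Statistical methods:** "Group comparisons on all outcome measures will be made at 14 weeks and approximately 35 weeks after the start of the intervention", and again at 2 years. Mixed models or repeated-measures ANOVA are planned for change over time, post hoc analyses are to be corrected for multiple comparisons where suitable, and the significance level is 0.05.

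**The concern.** A main hypothesis should be tested at the primary endpoint. Here the time point of the main hypothesis is the one labelled secondary. Read from the Abstract, the trial is decided at about 35 weeks and 2 years is supportive. Read from the objectives, it is decided at 2 years.

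The two readings diverge when the results do. If the groups differ at 35 weeks but not at 2 years, the authors could report that the primary endpoint was met or that the main hypothesis was not supported. The opposite pattern leaves the same choice.

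The 35-week data also come first. With inclusion from 3 to 8 months of age (Abstract) and 35 weeks being about 8 months, that visit falls at roughly 11 to 16 months of age, some 8 to 13 months before the 2-year visit. The Sample size section also announces continuous interim analysis. The ranking could thus end up being settled with group results in view.

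**Working it through.** **1. Side-by-side reading**

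| Section | Time point(s) | Rank given |
|---|---|---|
| Abstract, Method and design | about 35 weeks; 2 years | primary; secondary |
| Primary and secondary objectives | 2 years | main hypothesis |
| Methods and design | 14 weeks; about 35 weeks; 24 months | none |
| Sample size | not stated | none |
| Outcome measures and procedures | not stated | none (PDMS-2 is the primary measure) |
| Statistical methods | 14 weeks; about 35 weeks; 2 years | none |

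Only the first two rows rank anything, and they disagree. The sample size cannot break the tie. It names no visit, and without a standard deviation the figure of 15 per group cannot be reproduced. Fig. 1 is not available to me, but a label in it could not make both sentences true.

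**2. Size of the consequence**

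The plan gives no figure to reproduce on this point, so this is an illustration.

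Inputs:
- Significance level 0.05 per test, from Statistical methods. Sidedness is not stated; two-sided is assumed, so the critical value is 1.96.
- Two test statistics, Z35 and Z2y, bivariate normal with mean 0 under no true effect and correlation r. The document gives no r; the assumed range is 0 to 0.9.
- No adjustment between the two tests, because none is specified for this pair.

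Formulas:
- At least one significant: A = 1 − P(|Z35| < 1.96 and |Z2y| < 1.96). At r = 0, A = 1 − 0.95² = 0.0975.
- Both significant: B = 0.05 + 0.05 − A.
- Exactly one significant: E = A − B = 2A − 0.10. At r = 0.9, E = 2 × 0.0704 − 0.10 = 0.0407 (unrounded A is 0.07035).
- At least one significant in favour of Small Step: F = 1 − P(Z35 < 1.96 and Z2y < 1.96). At r = 0, F = 1 − 0.975² = 0.0494.

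| r (assumed) | A: at least one | E: exactly one | F: at least one favouring Small Step |
|---|---|---|---|
| 0 | 0.0975 | 0.0950 | 0.0494 |
| 0.5 | 0.0907 | 0.0815 | 0.0454 |
| 0.7 | 0.0835 | 0.0669 | 0.0417 |
| 0.9 | 0.0704 | 0.0407 | 0.0352 |
| One pre-named test | 0.05 | – | 0.025 |

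**3. Small-sample check**

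Taking 24 per group less 20% drop-out gives 24 × 0.8 = 19.2, so 19 per arm (an assumption; the 20% is the rate in the Sample size section). A simulation with t tests, 200,000 runs, gave A = 0.097, 0.091, 0.084 and 0.071 at r = 0, 0.5, 0.7 and 0.9. The normal approximation is adequate.

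**The case against.** The best defence is that only the Abstract uses the terms primary and secondary endpoint, and it uses them clearly. The objectives state a hypothesis, not an endpoint. One could read 35 weeks as the primary endpoint and the 2-year hypothesis as the long-term aim. That reading is coherent, but the article does not state it, and it would leave the declared main hypothesis without a confirmatory test.

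A second defence is that Statistical methods provides for correction for multiple comparisons. It does so for post hoc analyses and only where suitable. It does not choose between the two times or divide the 5% between them.

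A third is that the figure, the registration or a fuller protocol may rank the time points. That could limit how far the main result can be chosen later, and I cannot rule it out. It would not remove the conflict from the article, which does not leave the point open for another document but states it twice and differently.

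Three parts of the case against do stand:
- The error rates describe what happens if the choice follows the results. They are not the error rate of any rule written in the plan.
- The main hypothesis names no measure, so treating both tests as PDMS-2 comparisons is an assumption.
- Which time point should decide is a scientific choice for the investigators. A fixed testing order is as acceptable as demoting the 2-year comparison.

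**Conclusion.** The concern holds. The article contradicts itself on the deciding time point, and nothing else in the shown text resolves it. This part rests on the wording alone and needs no assumption.

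The size is conditional. If either comparison can be presented as the main result, the false-positive rate rises from 5% to between 7.0% and 9.75%, and the chance of a false claim for Small Step from 2.5% to between 3.5% and 4.9%. Those ranges assume correlations of 0.9 down to 0, two-sided tests and no adjustment between them. In 4.1% to 9.5% of trials with no true effect, the two sections would give opposite verdicts.

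The investigators should correct this. It does not affect the conduct of the trial, but it does determine what the trial can claim.

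**What to change.** Name one deciding comparison, use it in all three places, and do so before any outcome is compared by group.

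**Simplest option: keep the Abstract's ranking.**
- In Primary and secondary objectives, reword the main hypothesis along these lines: *Our main hypothesis is that PDMS-2 results about 35 weeks after starting the intervention are better with Small Step than with usual care; superiority at 2 years is a secondary, longer-term hypothesis.*
- In Statistical methods, add: *The primary comparison is PDMS-2 at about 35 weeks; the 14-week and 2-year comparisons are secondary.*

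This costs one reworded and one added sentence, with no extra visits, measures or children. The price is that lasting benefit at 2 years is no longer a confirmatory claim.

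**Equally acceptable: a fixed order.** Test PDMS-2 at about 35 weeks at 5%, and test 2 years at 5% only if the first test is significant. This holds the overall error at 5% and keeps a confirmatory 2-year claim, which is lost if the 35-week test fails. It needs the order written into both the objectives and the statistical methods.

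**Making 2 years primary** is also possible, as that visit is already planned. It reverses the order in the Abstract and delays the main result until the last child reaches 2 years.
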